# Augmentation effect of acupuncture on Bi’nao for hypophasis in patients with Bell’s palsy: study protocol for a randomized controlled trial

**DOI:** 10.1186/s13063-018-2699-z

**Published:** 2018-06-11

**Keywords:** Acupuncture, Hypophasis, Bell’s palsy, Facial paralysis

## Abstract

**Background:**

Hypophasis is one of the most frequently observed sequelae of patients with Bell’s palsy, who have not recovered completely, creating a clinical difficulty for physicians. Acupuncture therapy has been widely used to treat Bell’s palsy as a reasonable resolution for management of symptoms such as hypophasis. The number of acupuncture points (acu-points) is frequently selected in the approach of acupuncture therapy; however, whether these had high efficiency has not been proved. According to the literature review, Bi’nao was useful for treating eye and eye lipid diseases, which could be proved only by some successful cases. Thus, a randomized controlled trial was designed to evaluate the efficiency of the acu-point Bi’nao.

**Methods/Design:**

Participants with hypophasis as the major symptom are selected among patients with Bell’s palsy and randomly allocated into one of the three groups at a 1:1:1 allocation ratio. All participants receive conventional acupuncture therapy; however, those assigned to the real acupuncture group will be given added acupuncture therapy on the acu-point Bi’nao, while those assigned to the sham acupuncture group were given extra acupuncture therapy on the sham Bi’nao as a placebo. The efficacy of the acupuncture therapy on the acu-point Bi’nao for hypophasis will be evaluated by Eye Crack Width Measurement (ECWM) and Eyelid Strength Assessment (ESA) before and after therapy.

**Discussion:**

This is the first study assessing the safety and efficiency of Bi’nao in treating the hypophasis of patients with Bell’s palsy that might support the application of this acupuncture therapy. However, evaluating hypophasis is challenging, and, thus, ECWM and ESA were applied to measure the eyelid movement.

**Trial registration:**

Chinese Clinical Trials Registry, ChiCTR-INR-17012955. Registered on 12 October 2017.

**Electronic supplementary material:**

The online version of this article (10.1186/s13063-018-2699-z) contains supplementary material, which is available to authorized users.

## Background

Bell’s palsy is a type of self-limited peripheral neuropathy with uncertain pathogens. Patients with Bell’s palsy suffer from dysfunction of the facial nerve and inflexible muscle movements; the majority of them will recover within 1–3 months. However, a few of them will undergo a long recovery procedure and/or leave some sequelae such as deviation of mouth angle, hemifacial spasm, or hypophasis [1, 2].

Hypophasis is frequently observed among some patients with Bell’s palsy, who are almost at complete recovery, and is occasionally accompanied with a tiny droopy corner of the mouth, which is the major obstacle before full recovery from Bell’s palsy, as well as posing huge difficulties for doctors or rehabilitation physicians. The syndrome of hypophasis will continue to maintain the status quo unless appropriate therapy is applied; however, over-treatment such as excessive exercise or transcutaneous electrical nerve stimulation may lead to facial spasm [3, 4].

Acupuncture therapy has been widely used for the treatment of Bell’s palsy in China and worldwide [5–8]. Although the efficacy of the therapy has not been sufficiently proved by systematic reviews [9], its application has been considered a reasonable resolution for the management of some symptoms such as hypophasis. Although acu-points around the eye socket are frequently selected in the approach of acupuncture therapy, high-efficiency widely accepted acu-points have not yet been reported.

However, Bi’nao, an acupuncture point located on the large intestine meridian of the hand Yangming was found to be useful for treating hypophasis. The therapeutic effect of this acu-point was first reported in the book *Zhenjiu Jiayi Jing*, A-B classic of Acupuncture and Moxibustion [10]. Bi’nao is localized at the connection of the large intestine meridian of the hand Yangming and the collaterals of the hand Yangming. According to the records of *Huangdi Ming Tang Jing*, the collaterals of the hand Yangming is a critical joint of the small intestine meridian of the hand Taiyang, the bladder meridian of the foot Taiyang and Yangwei Channel. These four meridians are linked to the eye, and hence, acupuncture could be performed on Bi’nao for treating the eye and eye lipid diseases as described previously [11–19]. This acu-point was also used in our clinical practice for treating ophthalmoplegia and hypophasis; however, its efficacy could not be proved by a few successful cases. Thus, a randomized controlled trial (RCT) was designed to evaluate its efficiency compared to a placebo point.

## Methods/design

### Objective

The present study assessed the augmenting effect of acupuncture therapy on the acu-point Bi’nao for hypophasis through eye crack width and eyelid strength compared to a sham acu-point and no acupuncture treatment on Bi’nao.

### Design and setting

This study is a single-center, three-arm, patient-blinded and assessor-blinded (to the type of acupuncture treatment), parallel-group, RCT conducted in China. The results followed the Consolidated Standards of Reporting Trials (CONSORT) guidelines as well as Standards for Reporting Interventions in Clinical Trials for Acupuncture (STRICTA) [20] and Standard Protocol Items: Recommendations for Interventional Trials (SPIRIT) guidelines [21]. This study (protocol version 1.0, 30 June 2017) has been registered at the Chinese Clinical Trials Registry (ChiCTR-INR-17012955). Figure 1 shows the research design and Additional file 1 displays the complete SPIRIT checklist.

**Fig. 1 Fig1:**
[figure not shown]
*Schematic* representation of the study design

### Recruitment period

The participants will be recruited from the Department of Acupuncture, Baoshan Hospital of Integrated Traditional Chinese Medicine and Western Medicine, Shanghai, China. The recruitment is expected to span from September 2017 to March 2020.

### Methods of recruitment

A total of 99 participants diagnosed with Bell’s palsy and mainly suffering the symptom of hypophasis through the outpatient or inpatient department will be recruited at the Department of Acupuncture, Neurology, and Geratology, Baoshan Hospital of Integrated Traditional Chinese Medicine and Western Medicine, Shanghai. The participants will be recruited by posters displayed in the hospital registration hall and brochures sent out to the visitors of those departments. The study title, research target, period, location, and contents of the intervention will be introduced to the participant.

### Study setting

The research assistants will obtain written consent (version 1.0, 30 June 2017) from the patients potentially eligible for the study. A researcher will explain the manipulation of acupuncture treatments used in traditional Chinese medicine (TCM) clinics. Subsequently, a researcher will screen whether the patient can participate in the study. If the patient fulfills the inclusion/exclusion criteria, a clinical research coordinator (CRC) specified by the scientific research department, Baoshan Hospital of Integrated Traditional Chinese Medicine and Western Medicine, Shanghai will contact an independent researcher who has the random number table; the participants will be randomly allocated into one of the three groups (group A, B, or C) at a 1:1:1 allocation ratio. All participants will receive conventional acupuncture therapy; however, the participants assigned to group A will be given additional acupuncture on the acu-point Bi’nao, while the participants assigned to group B will be given extra acupuncture on a point 1 cm backward to Bi’nao as a placebo point. Only group C participants will not receive extra acupuncture on any other acu-point.

The participants of this trial will undergo acupuncture treatments three times a week for one month. The Eye Crack Width Measurement (ECWM) and Eyelid Strength Assessment (ESA) of all the participants will be performed at the allocation time point, weekly during the treatment duration, and one month after the first therapy. The first ECWM and ESA value will be recorded as a baseline and the final values will be recorded as the end-time measurement. The follow-up visits for all participants will be scheduled at three months after the first acupuncture therapy. After the participants have completely recovered from hypophasis, the acupuncture therapy will be stopped and the final ECWM and ESA values will be recorded as an end-time measurement.

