### Intervention

#### Acupuncture treatment

Acupuncture will be performed by specialists in TCM and follow the STRICTA 2010 checklist (Table 1).

**Table 1 Tab1:** Details of acupuncture intervention (according to the Standards for Reporting Interventions in Clinical Trials of Acupuncture (STRICTA) 2010 guidelines Expansion of Item 5 from Consolidated Standards of Reporting Trials 2010 guidelines)

Acupuncture rationale	Style of acupuncture	Traditional Chinese Medicine
	Rationale for treatment	Acupuncture has been historically used to treat hypophasis in facial palsy. Additionally, it is known to be a safe treatment used in a wide range of symptoms caused by Bell’s palsy
	Extent to which treatment varied	The participants in the intervention group all receive the same manual acupuncture treatment
Details of needling	Number of needle insertions per individual per session	8–9
	Names of the insertion points (uni/bilateral)	BL2, GB14, SJ23, Shangming, LI14 (unilateral, affected side); SJ5, KI6(bilateral)
	Depth of insertion	10–30 mm (exact depth shown in Table 2)
	Response sought	De-qi
	Needle stimulation	Manual stimulation (exact details are in the text)
	Needle retention time	20 min
	Needle type	0.30 mm (diameter) × 25 mm (length) disposal needle (Huatuo Acupuncture Inc., Suzhou, China)
Treatment regimen	Number of treatment sessions	12
	Frequency and duration of treatment sessions	3 sessions per week for 4 weeks
Other components of treatment	Details of other interventions administered to the acupuncture group	No other interventions are done
	Setting and context of treatment	All participants are informed that they will receive acupuncture treatment, which can potentially reduce symptoms of hypophasis; however, the control group will have to complete the evaluations during the first week before receiving the same treatment as the acupuncture group
Practitioner background	Description of participating acupuncturists	Specialists in TCM with at least 3 years of practice in acupuncture
Control or comparator interventions	Rationale for the control or comparator in the context of the research question	Sham acu-point is used as a placebo control
	Precise description of the control or comparator	Placebo control group be given extra acupuncture on a point 1 cm backward to Bi’nao as a placebo point

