### Outcome measures

#### Primary outcome

ECWM will be performed using a graduated ruler to measure the width (mm) between the upper and lower eyelids when the patients attempt to close his eyes. The measurements will be taken three times and the average recorded. ECWM will be performed before acupuncture therapy as the primary time measurement, weekly during the treatment duration, and at the first month after the first therapy by three physicians, and the average value recorded. The mean value and standard deviation among the participants in every group will be calculated; the differential values of eye crack width (mm) between the intervention and control groups will be compared.

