#### Follow-up

All participants will be followed up at three months after the first acupuncture therapy, including those who completely recovered from hypophasis within one month. The follow-up will be accomplished by a clinic visit or telephone survey about the progress and recurrence of hypophasis.

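### For patients who recover early, the protocol gives two candidate primary ECWM values, one at recovery and one at one month, and does not say which is analysed

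*Protocol article*

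**What the plan says.** Three sections of the protocol article bear on this.

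- **Study setting, general rule.** One schedule covers both ECWM and ESA (Eyelid Strength Assessment): the measurements "of all the participants will be performed at the allocation time point, weekly during the treatment duration, and one month after the first therapy". Baseline is the initial reading, and "the final values will be recorded as the end-time measurement".
- **Study setting, early recovery.** The last sentence adds a second rule for patients who recover completely: "acupuncture therapy will be stopped and the final ECWM and ESA values will be recorded as an end-time measurement".
- **Primary outcome.** ECWM is taken before therapy, "weekly during the treatment duration, and at the first month after the first therapy by three physicians". No exception is made for patients whose therapy has stopped.
- **Follow-up.** This section states: "All participants will be followed up at three months after the first acupuncture therapy, including those who completely recovered from hypophasis within one month". Contact is by "clinic visit or telephone survey about the progress and recurrence of hypophasis"; ECWM is not mentioned.

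**The concern.** A patient who recovers in, say, the second week has two readings that could each be the end-time value: the one when therapy stops and the one at one month. The protocol creates both and does not choose. Two analysts following the text faithfully could compute different primary results from the same data.

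The choice matters because complete recovery is the outcome under study. If the recovery-time reading is used, a good result triggers the measurement, and everyone else is read at one month. Should one arm recover faster, more of its values are fixed at a favourable moment. A gap that reopens before one month would then not count against that arm in the primary comparison.

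The situation is foreseen in the plan itself: the Follow-up section provides for patients who recover within one month and asks about recurrence.

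**Working it through.** **1. The passages side by side.**

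| Patient | Study setting, general rule | Study setting, early-recovery rule | Primary outcome |
|---|---|---|---|
| Not recovered by one month | one-month value | does not apply | one-month value |
| Recovered earlier | one-month value (schedule covers all participants) | value when therapy stops | one-month value (no exception) |

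Only the second row conflicts. The weekly readings are tied to the treatment period, so on the written schedule they end when therapy stops. The one-month visit is then the only remaining ECWM that could show an early relapse.

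**2. The plan's own figure.** Under Sample size calculation the inputs are a difference of 2 points, SDs of 1 and 3, two-sided α of 0.05 and 90% power:

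(1.96 + 1.28)² × (1² + 3²) / 2² = 26.24, rounded up to 27 per group.

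This reproduces the stated minimum. With a common SD of √((1 + 9)/2) = √5, a two-sided two-group comparison at 27 per group has 90.8% power. Nothing here disputes the sample size.

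**3. Possible size of the bias.** For groups A and C (any other pair works the same way):

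bias = (pA − pC) × r × g

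Here pA and pC are the shares recovering before one month, r is the share of those who relapse by one month, and g is their mean reopened gap in mm. The documents give none of these, so all are assumptions. One point of ECWM is taken as 1 mm.

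| Case | pA | pC | r | g (mm) | Bias (mm) | Share of 2 |
|---|---|---|---|---|---|---|
| No relapse | any | any | 0 | any | 0 | 0% |
| Low | 0.3 | 0.1 | 0.05 | 1 | 0.20 × 0.05 × 1 = 0.01 | 0.5% |
| Middle | 0.5 | 0.2 | 0.10 | 2 | 0.30 × 0.10 × 2 = 0.06 | 3% |
| High | 0.6 | 0.2 | 0.30 | 3 | 0.40 × 0.30 × 3 = 0.36 | 18% |

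The bias favours the arm with more early recovery.

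**4. What this means on the one-month scale.** If the difference were 2 with recovery-time values, the one-month difference would be 2 − 0.01 = 1.99 (low case) to 2 − 0.36 = 1.64 (high case). With 27 per group and the same SD, power to detect it would be 90.5% to 76.9%.

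**The case against.** The strongest reply is that the protocol already measures everyone at one month. The early-recovery sentence records **an** end-time measurement, where the general rule speaks of **the** end-time measurement, and it nowhere says that the recovery value replaces the later one. A reader might infer that the one-month value is overridden. The text does not establish that, so the point has to be put as an unresolved conflict. That conflict stands, because the same term is attached to two different readings.

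Three other stronger readings are tempting and are not supported:

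- **Relapse is never counted.** The three-month contact covers all participants, including early recoverers, and asks about recurrence. What stands is narrower: an early relapse would not enter the primary ECWM value, and a contact that may be by telephone, with no ECWM named, cannot correct it.
- **An unblinded therapist decides when the endpoint is taken.** Randomization and blinding does say that the treating doctors know the allocation, but no section says who declares recovery. The assessors are blinded, and recovery could equally be read from the weekly assessments.
- **Recovery is undefined, and that is itself a flaw.** A numerical criterion is operational detail that an article may leave to the full protocol. It is not part of this point.

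It is also fair to say that mixed time points alone do little harm. A fully closed eye cannot improve on ECWM, so the recovery value equals the one-month value unless the gap reopens. The high case is generous: three in ten early recoverers would have to relapse within weeks, to a mean gap of 3 mm, when a gap above 2 mm was enough for entry.

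**Conclusion.** The conflict is real and concerns the primary endpoint. Study setting gives early recoverers an end-time value at the point where therapy stops; Study setting and Primary outcome also schedule a one-month value for everyone; which one is primary is not stated. If the recovery-time value is used, the time point depends on the outcome, can differ by arm, and leaves out relapse before one month.

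Whether this biases the result materially is not known. The bias is zero without early relapse. On the assumed inputs it is about 0.01 to 0.36 mm, or 0.5% to 18% of the planning difference, and only the more extreme assumptions reach the upper end. The case for acting rests on the ambiguity and the low cost of removing it, not on a demonstrated large bias.

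**What to change.** Reconcile Study setting with Primary outcome in one sentence: the primary value is the ECWM at the fixed one-month visit, read by the blinded assessors, for every randomised patient, whether or not therapy stopped early. Keep the recovery-time ECWM as a secondary variable.

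The cost is a wording change and attendance by early recoverers at a one-month visit that is already scheduled. The planned sample size stays as it is. If relapse does occur, the one-month difference will be somewhat smaller than the recovery-time one.

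Trial status describes recruitment as ongoing, so the choice should be recorded while the data are still blinded. If any patient already treated has no one-month reading because therapy stopped early, the number by arm should be reported.

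The change settles only which measurement is analysed and takes no position on when treatment should stop.

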### Participants

The selected outpatients and inpatients are from the Departments of Acupuncture, Neurology, and Geratology of Baoshan Integrated Traditional Chinese Medicine and Western Medicine Hospital, Shanghai, China. Both male and female patients (age range = 18–60 years) are enrolled. All the patients are randomized into either Group A (acupuncture on the acu-point Bi’nao), Group B (placebo acu-point), or Group C (none acupuncture on the acu-point Bi’nao).

### Inclusion criteria

Patients with Bell’s palsy, who fulfilled the following inclusion criteria, will be enrolled in the study: unilateral facial paralysis; aged 18–60 years; Bell’s palsy onset > 1 month but < 3 months; most symptoms recovered but hypophasis was present; the distance between the upper and lower eyelids was > 2 mm; and those with negative pathological signs.

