## Discussion

The present study evaluated the efficacy of acupuncture therapy on the acupoint Bi’nao for hypophasis in patients with Bell’s palsy based on the previous studies and our clinical experience. When planning a manual acupuncture study, the duration of treatment, treatment points, and frequency of stimulation should be considered as these can affect the outcomes of acupuncture. However, in a RCT, only one variable could be tested. Thus, we established this regimented acupuncture protocol that has been discussed and optimized at the Baoshan Hospital of Integrated Traditional Chinese Medicine and Western Medicine, Shanghai.

In addition, the function of “De qi” will be considered in the trial; it is based on subjective reporting of the patient (soreness, numbness, fullness, radiating sensation) and is regarded as a sign of efficacy according to TCM. A majority of the contemporary acupuncturists still seek “De qi,” rendering it as fundamental to efficacy. The placebo effect produced by sham acupuncture was considered to influence the disease lightly, although needle pricking might induce non-specific physiological reactions. The sensation of “De qi” can be accurately described by sense felt by either the practitioner or patient, and reliable scales such as the Massachusetts General Hospital Acupuncture Sensation Scale (MASS) have already been applied in clinics measuring the intensity of “De qi” sensation [24–26].

The assessment of hypophasis is rather challenging due to the lack of a widely recognized method or scale. The House-Brackmann scale and Sunnybrook Grading System are suitable for the overall assessment of Bell’s palsy, but are not applicable to individual symptoms such as hypophasis. Thus, we created the ECWM and ESA to evaluate eyelid movement according to some neurological function classification. Although this was an innovative approach, it was also a limitation of this study.

The results showed that the acupuncture treatment on the acu-point Bi’nao is a safe and effective method for improving hypophasis. Furthermore, the study provided evidence to support the application of acupuncture therapy in the management of Bell’s palsy and its sequelae in the future.

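### The entry window matches the article's own 1–3 month recovery period, so the conclusion should be limited to residual hypophasis at that stage and the analysis should adjust for time since onset

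*Protocol article*

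**What the plan says.** The Inclusion criteria require "Bell’s palsy onset > 1 month but < 3 months; most symptoms recovered but hypophasis was present", together with unilateral paralysis and an eyelid gap above 2 mm. No reason for the onset window is given.

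The Background speaks first of the disease: "Bell’s palsy is a type of self-limited peripheral neuropathy with uncertain pathogens". Of its patients it says that "the majority of them will recover within 1–3 months", and that "a few of them will undergo a long recovery procedure and/or leave some sequelae such as deviation of mouth angle, hemifacial spasm, or hypophasis". It then turns to the symptom: "Hypophasis is frequently observed among some patients with Bell’s palsy, who are almost at complete recovery", and "The syndrome of hypophasis will continue to maintain the status quo unless appropriate therapy is applied". The Abstract starts from the same idea: "Hypophasis is one of the most frequently observed sequelae of patients with Bell’s palsy, who have not recovered completely".

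The Objective section asks for the added effect of needling Bi'nao on hypophasis, compared with a sham point and with no needling there. It sets no minimum duration of hypophasis. The Randomization and blinding section describes 1:1:1 block randomisation. The Statistical analysis section names a one-way ANOVA of ECWM and ESA across the groups, with a Kruskal–Wallis test for non-normal data. The Discussion ends by saying that "the study provided evidence to support the application of acupuncture therapy in the management of Bell’s palsy and its sequelae".

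**The concern.** The rationale is a residual deficit that persists after the palsy has otherwise resolved. The entry rule takes patients only from the interval in which the article expects most palsies to resolve, and closes at the point where a remaining deficit could most safely be called a sequela. The criteria as printed ask for no period of stability or repeat measurement before entry, so they do not separate a settled deficit from a recovery still under way.

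Two things are at stake. The first is the conclusion: a difference found between 1 and 3 months after onset may reflect faster closure in patients who would have closed anyway, and that is not evidence about established sequelae. The second is sensitivity: if some patients in every arm recover regardless of allocation, the contrast between arms may shrink. Time since onset is a plausible marker of where a patient stands in that course, and the analysis named in the article makes no use of it.

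**Working it through.** **The plan's own figure.** The Sample size calculation assumes SDs of change of 1 and 3 points, a difference of 2 points, two-sided α = 0.05 and 90% power:

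n = (1.96 + 1.28)² × (1² + 3²) / 2² = 10.4976 × 10 / 4 = 26.24 per group, printed as 26 and taken up to 27.

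This reproduces. The section mentions no allowance for recovery that is independent of arm.

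**Timing.** I assume that the first treatment closely follows allocation.

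- Entry: more than 1 and less than 3 months after onset.
- End measurement, one month after first treatment: about 1 + 1 = 2 to 3 + 1 = 4 months after onset. Anyone who enters before 2 months is still inside the 1–3 month period at the primary endpoint. The article does not give the distribution of entry times, so that share is unknown.
- Follow-up, three months after first treatment: about 1 + 3 = 4 to 3 + 3 = 6 months after onset. This lies beyond the recovery period, but it is described as a clinic visit or telephone survey on progress and recurrence, with no ECWM stated.

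The objective measurement is therefore stated only up to about 4 months after onset.

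**Dilution, as an illustration only.** The document gives no recovery rate for hypophasis. Suppose a fraction r in every arm recovers whatever the allocation and contributes no treatment difference, the 2-point effect applies to the rest, and the SDs stay as planned. Then the difference is δ = 2(1 − r). With 27 evaluable per arm, SE = √((1 + 9)/27) = 0.609 and power = Φ(δ/SE − 1.96):

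- r = 0: δ = 2.0, power 90.8%, 27 per arm for 90% power
- r = 0.1: δ = 1.8, power 84.1%, 33 per arm
- r = 0.2: δ = 1.6, power 74.8%, 42 per arm
- r = 0.3: δ = 1.4, power 63.3%, 54 per arm
- r = 0.5: δ = 1.0, power 37.6%, 106 per arm

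The Background's statement that hypophasis does not change untreated corresponds to r = 0. If the planned 2 points is already an average over patients who would recover anyway, there is again no loss. The list shows the direction and how steep the loss could be. It is not an estimate for this trial.

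**What the analysis can use.** A one-way ANOVA has group as its only factor and takes no covariate. Time since onset must be established for every patient to apply the inclusion criterion, and the baseline ECWM and ESA are recorded at allocation. Both are available at no extra effort, and the named method uses neither as a covariate.

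**The case against.** The strongest reply is that the article does not confuse the disease with the symptom. The 1–3 month statement is about Bell's palsy as a whole. About hypophasis the same section says that it stays unchanged without therapy. The criteria then pick patients whose other symptoms have mostly gone while a gap above 2 mm remains, which is the group the Background describes as almost recovered. The Background sets no three-month threshold for a sequela. On this reading the enrolled patients have reached a plateau. That reading is as open as the other one, and it is why no size can be put on the dilution.

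A reader might infer that the trial cannot answer its question. The document does not support that. The Objective concerns hypophasis without a duration limit, all arms receive the same basic acupuncture, and concurrent randomisation makes natural recovery equal across arms in expectation. The outcome sections specify comparisons between groups, so improvement common to all arms does not bias them.

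A reader might also want to express chance imbalance in onset time as millimetres of eyelid gap. That needs a rate of closure per month, which the document does not give. The test's type I error already covers chance imbalance, and onset-time variation is part of the SD of change used for the sample size. Nor does it follow that the block list must be stratified: unstratified block randomisation is valid, and stratification is an option.

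Finally, covariates are often left to an analysis plan. That would answer a complaint that the article is silent, but here it names a specific method that cannot take covariates.

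**Conclusion.** The point holds in limited form. The entry window coincides with the article's own recovery period and shuts out patients at three months or later, so the Abstract, Background and Discussion speak of sequelae more broadly than the Inclusion criteria allow. The comparison between arms is sound for the stated objective. What it can show is an effect on residual hypophasis 1–3 months after onset; taken alone, it does not carry the Discussion's wording on sequelae.

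Natural recovery during the trial could dilute the difference and lower power, but it does not bias the comparison between arms. The amount cannot be determined from the document and would be nil if the Background's statement about untreated hypophasis is right. The gain from adjusting for time since onset likewise depends on how strongly it predicts closure, which is unknown. The change is worth making because it costs almost nothing.

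**What to change.** 1. In Statistical analysis, replace the one-way ANOVA of ECWM and ESA with a linear model (ANCOVA) of the end measurement, with terms for treatment group, the baseline value of the same measure, and days from onset to randomisation. Fix this before the data are unblinded.
2. Limit the conclusion to residual hypophasis 1–3 months after onset, and reconcile the sequela wording in the Abstract, Background and Discussion with the Inclusion criteria. A sentence giving the reason for the window would help.

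The cost is a slightly more complex model, with two covariates against 3 × 27 = 81 planned evaluable patients, and a narrower claim. No extra patients, visits or measurements are needed, and the eligibility criteria and the randomisation list can stay as they are.
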